### Ethics Approval, Trial Registration, and Informed Consent

Both the Makerere University School of Health Sciences Research Ethics Committee (reference No. 2018-054) and the Uganda National Council of Science and Technology (UNCST; reference No. HS 2672) granted ethics approval. The trial was registered at ClinicalTrials.gov (NCT04164433). Any important protocol deviations or adverse events (AEs) will immediately be communicated to the Research Ethics Committee, the UNCST, and ClinicalTrials.gov. Additionally, we will seek permission from the responsible personnel officer at every site.

Each participant will provide written consent prior to recruitment into the CRT and will receive a copy of the signed form. They will also be informed that their participation is voluntary and that they may withdraw from the study at any time. Furthermore, permission will be sought to audio-record and take notes during the interviews.

All disclosed HIV status results will remain confidential. The employers will be made aware that the results will remain confidential and that the workers are not under any obligation to disclose their results, especially in the event that this may lead to a loss of jobs for those who are found to be HIV positive. All original documents will be deposited in a secure locked cabinet and accessed only by the three investigators. The trial data set will not have any participant identifiers and will be stored in electronic password-protected files.

### Sample Size Determination

Sample size estimation is based on the primary outcome: proportion of men who take an HIV test. The main outcomes were at the participant level. Currently, approximately 55% of males in Uganda have taken an HIV test [34]. We hypothesize a 15% increase in HIV testing in the workplace HIVST group in comparison to the control group. We considered a two-sided α of .05 with a power of 80% to detect a significant change between both groups, a 1:1 allocation ratio between the intervention and control arms, a response rate of 90%, and a design effect of 1.399. We estimate a minimum total sample size of 548 participants, with 274 per arm. The proxy for design effect was picked from the proxy variable “Had taken an HIV test and obtained results in the past year” [35]. 

### Data Collection

#### Cluster Randomized Trial Flow

All participants will be provided with a list of nearby health facilities that are accredited to provide ART. Participants will be asked to propose three facilities that they would like to visit for a confirmatory test if found to be HIV positive (Figure 2).

**Figure 2 figure2:**
[figure not shown]
Cluster randomized trial flow diagram. HIVST: HIV self-testing; RDT: rapid diagnostic test.

#### Intervention Arm

Since 2014, the WHO has encouraged countries to implement pilot HIVST programs to evaluate this approach. We will, therefore, follow the WHO strategy on self-testing to pilot HIVST in the workplace [22] (Figure 3). The strategy steps are as follows:

Explain the HIVST procedure and how to interpret the self-test results.Demonstrate the HIVST procedure and the interpretation of the results.Provide any additional instructional materials using an HIVST video.Answer any questions raised by the potential participant.Issue the OraQuick HIVST kits for collection of a mouth swab; participants will test at home or at a venue of their choice.Participants will return the results to the trial team in one of the following ways that will be agreed upon when they receive the kit:A phone call to the study toll-free line.A picture of the test results sent via email, WhatsApp, Facebook, or another preferred social media app.Presentation of the test kit at the health facility.Participant self-reporting the results at the health facility.Provide a referral slip and further information on linking to further services for those who receive a reactive self-test result. Those who test negative will receive further information and a referral to HIV prevention services.Provide participants with a counselor’s phone number. They will be offered the option of a call-back to return the results within 3 days of testing. Participants will also be told to use this number if they have any difficulty and need support during and after testing. This is in line with a recommendation from a study in Nigeria [36], where more than half of the participants who tested HIV positive used the helpline for support.Each participant will receive a code and instructions on what to write in case he is positive and can send these results as a text message. For example, 2018-7TR9-122-S is the code for a positive reactive test, and 2018-7TR9-122-T is the code for the nonreactive test. These codes will be randomly generated for each participant to avoid coworkers being able to accidentally interpret another person’s results.Participants who do not return the HIVST results within 3 days shall be phoned. This is in line with the Ugandan Ministry of Health test-and-treat strategy [6]. They will have given prior consent to be contacted.

**Figure 3 figure3:**
[figure not shown]
HIV self-testing (HIVST) pathway.

#### Control Arm

Security personnel allocated to the control arm will receive standard-of-care HIV counseling and testing based on the Ugandan Ministry of Health guidelines [6], as follows:

The control arm of this study will be offered standard facility-based care using antibody-based rapid diagnostic tests (RDTs), which follow the approved serial testing algorithm in Uganda for people above 18 months of age [6] (Figure 4).Whole blood will be collected via finger stick and capillary sampling by a trained HIV nurse or counselor who will use a lancet and transfer the blood to the screening test kit using a capillary tube. The specimen will be tested immediately.The nationally approved algorithm for HIV testing is as follows:All participants will undergo the screening test using the Alere Determine HIV-1/2 test (Abbott).All participants who receive a reactive result will undertake a confirmatory test using the HIV 1/2 STAT-PAK test (Chembio Diagnostic Systems).All participants with a nonreactive confirmatory test result will undertake a tie-breaker test using the SD BIOLINE HIV-1/2 test (Abbott).Participants whose samples react using the tie-breaker test shall be retested after 14 days.Participants who test positive will receive a referral slip to nearby public and private health facilities to expedite linkage to treatment, care, and support services.Participants who test negative will receive a referral slip for HIV prevention services. The participants will be referred to one of five public health facilities within the district.Each participant will be provided with a counselor’s contact number for continued consultation.

**Figure 4 figure4:**
[figure not shown]
Serial HIV testing algorithm for testing persons over 18 months of age in Uganda.

### Linkage to Care or Prevention Services

The participants will be followed up at 1 month and 3 months to determine their linkage into prevention, treatment, or care.

#### Referral of Clients With a Confirmed HIV Diagnosis

Following confirmatory HIV testing, clients diagnosed with HIV will be referred to local HIV treatment facilities using a paper referral slip provided by the research team. Once a client presents to a health facility with a referral slip, they will receive a confirmatory test prior to ART initiation. This approach reduces the risk of misdiagnosing their HIV status and unnecessarily treating HIV-negative persons, which has ethical and health system implications and causes individuals to suffer needless psychological effects [6,37]. A copy of the referral slip will be retained by the research team for use during follow-up. Participants who test positive for HIV will be encouraged to take their referral slip to the referral facility where staff will have been trained to keep the referral documentation and mark the source of the referral during patient registration. The unit of evaluation (ie, the indicator for the outcome of linkage to care) will be defined by the facility’s HIV testing registration records and clinic records of ART initiation.

#### Referral of Clients Confirmed as HIV Negative

Following confirmation of an HIV-negative result, clients will be offered information about voluntary medical male circumcision (VMMC). Pre-exposure prophylaxis (PrEP), condom use, and partner notification will be offered as an option for those who are sexually active. They will also receive a referral slip for these services to refer them to the nearest public health facility of their choice from their company offices. As mentioned above, the clients who present at the health facility will also receive a confirmatory test. The unit of evaluation will be defined by HIV testing by the facility, VMMC, partner services, and PrEP records.

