### Study Outcomes

#### Overview

The primary outcome will be uptake of HIV testing. Secondary outcomes will include testing yield, proportion of participants initiating ART during the first 3 months following HIV test results, and proportion of participants linked to prevention services (ie, consistent condom use, VMMC, PrEP, and retesting for HIV).

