#### Secondary Outcome Assessment

The following outcomes will be reported in the clinical trial record [33]:

HIV status reporting—the proportion of participants who self-report HIV test results. This will be assessed via telephone call by participants to the trial toll-free line or via picture of the self-test result sent through any of the following electronic channels: study email, WhatsApp, or the study Facebook account. Further assessment will include the presentation of either the trial participant or the self-test at a health facility.Linkage into HIV care—the proportion of participants with positive results who link to a health facility for HIV care. This will be assessed by checking the clinic records from the selected HIV care and treatment facilities at 1 and 3 months.Initiation of ART—the proportion of participants who initiate ART. This will be assessed by checking clinic records or possession of an ART card. Data will be collected using a questionnaire at 1 and 3 months.Uptake of VMMC following HIVST—the proportion of previously uncircumcised participants who self-report VMMC at 1 and 3 months.Consistent condom use following HIVST—the proportion of participants who use a condom for each sexual encounter for 1 month. Condom use will be assessed through verbal reports from the participants. Participants will be followed up at 1 and 3 months.Uptake of PrEP by men who have sex with men (MSM)—the proportion of MSM who initiate PrEP at 1 and 3 months. In this study, MSM will indicate the behaviors that transmit HIV infection, rather than how individuals self-identify in terms of their sexuality [38].

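### For HIV-negative men, a facility HIV test may count as linkage to prevention; only HIVST men have an added reason to attend, so the comparison can be biased towards HIVST

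*Protocol article*

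**What the plan says.** **HIV-negative men.** The section Referral of Clients Confirmed as HIV Negative (Protocol article) states the indicator: "The unit of evaluation will be defined by HIV testing by the facility, VMMC, partner services, and PrEP records". Just before that it says: "As mentioned above, the clients who present at the health facility will also receive a confirmatory test". The Overview under Study Outcomes gives the secondary outcome as the "proportion of participants linked to prevention services (ie, consistent condom use, VMMC, PrEP, and retesting for HIV"). Statistical Analysis then plans a between-arm comparison of the proportion of HIV-negative men who take up prevention services.

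**Returning a result.** In the Intervention Arm section, two of the ways an HIVST participant may return his result are located at a facility: "Presentation of the test kit at the health facility" and "Participant self-reporting the results at the health facility". Under Secondary Outcome Assessment, facility attendance also counts towards HIV status reporting: "Further assessment will include the presentation of either the trial participant or the self-test at a health facility". In the Control Arm section, a nurse or counselor takes the specimen and it is tested at once, so a control man has no result to bring back.

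**HIV-positive men.** Referral of Clients With a Confirmed HIV Diagnosis defines linkage to care by the facility's "HIV testing registration records and clinic records of ART initiation". Secondary Outcome Assessment instead describes men with positive results linking to a facility for HIV care, checked in clinic records, and lists ART initiation as a separate outcome.

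**The concern.** The facility test is part of the pathway that the protocol lays down for men who present. If that test also scores as linkage, a man can be counted as linked to prevention without having taken VMMC, PrEP, partner services or condoms. That would matter little if men in both arms had the same reasons to attend. They do not: result return is a step of self-testing delivery, and part of it can take place at the facility. A delivery step could then appear as downstream benefit in one arm.

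Linkage is part of the stated aim and hypothesis of the trial. At stake is whether a difference in prevention linkage would mean that more men took up a service, or only that more men had a facility visit recorded.

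**Working it through.** **Step 1: the chain in the text.**

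1. Facility HIV testing is a listed indicator for HIV-negative men (Referral of Clients Confirmed as HIV Negative), and retesting is a listed component of prevention linkage (Overview).
2. Clients who present receive a test (same referral section).
3. HIVST men have two facility-based routes for returning a result (Intervention Arm). The primary outcome for that arm requires return of the used kit within 1 month (Primary Outcome Assessment), and presenting the kit at a facility is the only listed route that physically delivers it.
4. Control men have no such visit (Control Arm).
5. For HIV-negative men, no section separates a visit made to return a result from a visit made to take up a service.

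One link is missing: the protocol does not say whether one record suffices or several are needed.

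**Step 2: the plan's own figure.** The protocol gives no figure for linkage. Its sample size for the primary outcome reproduces: 55% v 70%, two-sided 0.05, 80% power and continuity correction give 176 per arm; 176 × 1.399 = 246.2; 246.2 / 0.90 = 273.6, hence 274 per arm and 548 in total. The issue lies in the outcome definition and not in that arithmetic.

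**Step 3: illustration of size.**

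Inputs from the protocol: 274 per arm, testing of 70% and 55%, design effect 1.399 (Sample Size Determination); HIV prevalence 6.3% (Background, a national figure). Assumed, because the protocol gives neither: true linkage L, equal in both arms, and the share f of otherwise unlinked HIVST men who attend only to return a result and are tested and credited.

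- Scored linkage in the HIVST arm = L + (1 − L)f; in control = L.
- With L = 0.10 and f = 0.10: 0.10 + 0.90 × 0.10 = 0.19, against 0.10.
- HIV-negative tested men, HIVST: 0.70 × 274 × 0.937 = 179.7. Control: 179.7 if 70% also test there, or 0.55 × 274 × 0.937 = 141.2 at the planned 55%.
- Effective numbers after dividing by 1.399: 128.5, and 128.5 or 100.9.
- z = (p1 − p2) / √[p̄(1 − p̄)(1/n1 + 1/n2)], with p̄ the pooled proportion.

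Results for 19% v 10%:

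- No allowance for clustering, 70% testing in both arms: z = 0.09 / 0.0371 = 2.42, p = 0.015. This is too optimistic for a cluster trial.
- Design effect applied, 70% in both arms: z = 0.09 / 0.0439 = 2.05, p = 0.04.
- Design effect applied, control testing 55%: z = 0.09 / 0.0476 = 1.89, p = 0.058.
- As the last, with 90% response as well: z = 0.09 / 0.0501 = 1.80, p = 0.07.

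Other assumptions, design effect applied:

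| L | f | Scored, HIVST v control | p, control testing 70% | p, control testing 55% |
|---|---|---|---|---|
| 10% | 20% | 28% v 10% | 0.0002 | 0.0007 |
| 20% | 10% | 28% v 20% | 0.13 | 0.16 |
| 20% | 20% | 36% v 20% | 0.004 | 0.008 |
| 30% | 10% | 37% v 30% | 0.23 | 0.27 |
| 30% | 20% | 44% v 30% | 0.02 | 0.03 |
| 50% | 20% | 60% v 50% | 0.11 | 0.13 |

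Each p-value is the one obtained if the observed proportions equal the expected ones. The true difference is zero in every row.

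**Step 4: HIV-positive men.** If either record named in the referral section suffices, a confirmatory test alone is linkage to care. If both are needed, linkage largely repeats ART initiation, which is its own outcome. Neither reading matches the Secondary Outcome Assessment wording exactly.

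**The case against.** A reader might infer that every man who walks into a facility is scored as linked. The documents do not say so. The listed records and components are joined by a conjunction, and no rule makes one test sufficient. The sentence on testing at presentation refers back to the preceding section, where the client arrives with a referral slip; no section says that a man who comes only to hand over a kit or report a result is tested. That section also has staff keep the slip and mark the referral source, which could help to identify visits, although it says this for men who test positive. These points stand, and they are why the finding is conditional.

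A reader might also infer that linkage as a whole rests on testing registers. It does not. Secondary Outcome Assessment defines VMMC, condom use, PrEP and ART initiation separately, and a result-return visit cannot score any of them.

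Nor is the credit confined to one arm. Control men also receive referral slips and could be credited on attendance. The Control Arm section calls its testing facility-based, while the Abstract places it at work premises; if control tests entered a facility register, the baseline test could be credited there too. HIVST men can also report by phone, picture or coded text, which limits the share who attend.

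Finally, retesting may fairly be called a prevention service, and the Abstract groups confirmatory testing with linkage into care. Both are legitimate choices. But a test given on presentation soon after a self-test does not show that a man sought retesting, so retesting needs to be shown separately.

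**Conclusion.** The concern holds in a limited form. For HIV-negative men, the text allows a protocol-provided facility test to count as linkage to prevention, and only the HIVST arm has an added, result-return reason to attend. The resulting bias in the prevention-linkage comparison would run towards HIVST. This rests on two things that the text leaves open: that one record is enough, and that men attending to return a result are tested.

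The size cannot be determined from the protocol. Under the mildest illustration (L = 10%, f = 10%) there is a spurious difference of 9 percentage points, borderline at p about 0.04 to 0.06 once clustering is allowed for. At f = 20% it is clear for L of 10% to 30%, but not for L of 50%. It would be wrong to conclude that a false positive result is assured.

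For HIV-positive men the finding is a definition to reconcile and not a demonstrated bias, since a confirmatory test is a real step after a reactive self-test.

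**What to change.** - In Referral of Clients Confirmed as HIV Negative and in the Overview of outcomes, score linkage to prevention from a post-enrolment record or report of a specific service (VMMC, PrEP, partner services, condom use), and state whether one service is enough.
- Report retesting as a separate outcome that excludes the confirmatory test given on entry and any test done at a result-return visit.
- Reconcile Referral of Clients With a Confirmed HIV Diagnosis with Secondary Outcome Assessment, so that a confirmatory test alone does not count as linkage to care. Report confirmatory testing on its own, apart from both linkage to care and ART initiation.

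The cost is small. The service records are already to be collected, so the change is mainly wording and coding, plus noting the reason for each facility visit. Reported linkage percentages will be lower.

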#### Permitted Concomitant Interventions

In addition to HTS, security personnel in both the intervention and control arms will receive identical additional services. These services were identified through a needs assessment that was conducted earlier [32]. The findings from that study reported that both employers and employees were more willing to undergo HIV testing at the workplace if this was provided in combination with other health promotion interventions as a way of mitigating stigma. The additional package will, therefore, include the following: a blood pressure assessment, blood glucose and BMI measurements, and an RDT for syphilis. The additional package will be offered to both the intervention and control groups prior to enrollment in the study. We do not expect these concomitant interventions to affect the results of the trial.

### Study Outcomes

#### Overview

The primary outcome will be uptake of HIV testing. Secondary outcomes will include testing yield, proportion of participants initiating ART during the first 3 months following HIV test results, and proportion of participants linked to prevention services (ie, consistent condom use, VMMC, PrEP, and retesting for HIV).

#### Primary Outcome Assessment

We are operationally defining uptake of HIV testing as accepting to take an HIV test from the standard-of-care services that will be offered to the control group or receiving and returning a used HIVST kit for the intervention group. The proportion of security personnel in the control group who take an HIV test will be computed by dividing the number of participants in the standard-of-care cluster who agree to take an HIV test by the total number of those enrolled in the control arm. For the participants in the intervention cluster, uptake of HIV testing will be computed by dividing the number of participants who return the used HIVST kit within 1 month from the time of the test kit distribution by the total number who enrolled in the intervention arm.

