## Discussion

This research project aims to evaluate the effects of HIVST on HIV care-seeking among men. One anticipated challenge of the HIVST intervention is how the researchers will confirm the participants’ HIVST results, as these will be self-reported. We propose the use of mobile phone apps, such as WhatsApp, that participants can use to send their results back for verification, but this may be a challenge for those without smartphones. Another anticipated challenge revolves around participants’ work schedules. The field employees in the private security companies may not be available for HTS on the days scheduled for data collection, which may delay recruitment and hinder achieving the desired sample size.

With 88% of PLHIV identified in Uganda, it is difficult to identify the remaining undiagnosed PLHIV with general population approaches. This project uses one of the recommended approaches called targeted testing, which focuses on an individual or group of individuals who are at high risk of HIV acquisition [6]. Men employed in private security companies represent an ideal population for targeted testing. They are considered among the priority populations with limited access to HTS due to the nature of their work, and their social migration puts them at risk of HIV [34]. Additionally, the WISe-Men trial will provide information regarding whether testing at worksites increases men’s engagement in HIV testing and linkage to post-HTS in Uganda. The trial results will be communicated to the participants, health care professionals, and the public through workshops and meetings and to other relevant groups through publications in peer-reviewed journals and conferences. The findings from this study will contribute to policy development regarding HIVST and will inform the future regional, national, and international implementation of HTS.

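### A self-test kit used by someone else and then returned counts as the enrolled man having tested; this error can arise only in the HIVST arm, although the endpoint's net bias is not fixed

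*Protocol article*

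**What the plan says.** All references are to the protocol article.

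- **Target quantity.** Sample Size Determination: "Sample size estimation is based on the primary outcome: proportion of men who take an HIV test". The Statistical Analysis section also compares the arms on the proportion taking a test.
- **HIVST scoring.** Primary Outcome Assessment defines uptake as "receiving and returning a used HIVST kit for the intervention group". The numerator is the men who "return the used HIVST kit within 1 month from the time of the test kit distribution", and the denominator is "the total number who enrolled in the intervention arm".
- **Where the kit is used.** Intervention Arm: "Issue the OraQuick HIVST kits for collection of a mouth swab; participants will test at home or at a venue of their choice". Each man receives a randomly generated code for reporting his result.
- **Control scoring.** Primary Outcome Assessment uses "accepting to take an HIV test from the standard-of-care services that will be offered to the control group", with the numerator "the number of participants in the standard-of-care cluster who agree to take an HIV test".
- **How control tests are done.** Under Control Arm, a trained nurse or counselor takes a finger-stick sample from the participant and it is tested straight away.
- **Acknowledged difficulty.** Discussion: "One anticipated challenge of the HIVST intervention is how the researchers will confirm" the self-test results, since these are self-reported. Use of the kit by another person is not mentioned.

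**The concern.** The trial is sized and analysed on whether a man takes a test, but the HIVST arm is scored on what happens to an object. A used kit shows that somebody was swabbed. The participant code shows whose kit it was, not whose mouth the swab went into. A man who does not test, passes the kit to a partner or coworker and brings it back meets the stated rule in full.

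In the control arm the enrolled man is the person sampled, so this misclassification differs by arm and, on its own, favours HIVST. Another person's result could also enter the man's reported HIV status, and so affect who is counted as reactive. Linkage and ART initiation are less exposed, because they draw on clinic records and men who present at a facility are tested again.

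**Working it through.** **1. Reproduce the plan's figure.** Inputs from Sample Size Determination: 55% control uptake, a 15% increase (read as 15 points, to 70%), two-sided α .05, 80% power, design effect 1.399, response rate 90%.

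- Pooled two-proportion formula with mean proportion 0.625: n = [1.960·√(2·0.625·0.375) + 0.842·√(0.55·0.45 + 0.70·0.30)]² / 0.15² = 162.3.
- Continuity-corrected: 175.4, rounded up to 176.
- 176 × 1.399 = 246.2, and 246.2 / 0.90 = 273.6, so 274 per arm and 548 in total. This matches the protocol.

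**2. Size of the error taken alone, with no true effect.** Let true uptake be 55% in both arms. Let g be the share of non-testers whose kit is used by someone else and returned. The article gives no value, so g is assumed.

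- Scored HIVST uptake = 0.55 + 0.45·g.
- Effective n per arm = 274 / 1.399 = 195.9.
- The chance of p<.05 uses the pooled two-proportion z-test, both tails. For g = 0.10 the difference is 0.045, the standard error under the null is 0.04999 and under the alternative 0.04994. The upper tail is P(Z > (1.960 × 0.04999 − 0.045) / 0.04994) = P(Z > 1.061) = 14.4%. The lower tail adds 0.2%, giving 14.6%.

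| g (assumed) | Scored HIVST uptake | Spurious difference | Chance of p<.05 |
|---|---|---|---|
| 0 | 55.0% | 0 | 5.0% |
| 5% | 57.25% | +2.3 points | 7.3% |
| 10% | 59.5% | +4.5 points | 14.6% |
| 20% | 64.0% | +9.0 points | 44.2% |

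If the 90% response rate is also applied (effective n = 274 × 0.9 / 1.399 = 176.3), the last column becomes 7.1%, 13.7% and 40.5% for the three non-zero rows.

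**3. Net direction.** The Intervention Arm section also lets men report by phone, picture, text code or self-report at a facility, and none of these hands in a kit. Let u be the share of true testers who do not return a kit within 1 month. With true uptake of 70%, scored uptake = 0.70·(1 − u) + 0.30·g.

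- g = 10%, u = 0: 73%, above the truth.
- g = 0, u = 10%: 63%, below the truth.
- g = 10%, u = 10%: 66%, below the truth.

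The error from another user pushes upward, but the scored value can end on either side of true uptake.

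**The case against.** The strongest objections, and what stands of each:

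- **A reader might infer that the endpoint must overstate the HIVST effect.** The document does not support that. The same scoring rule counts as untested any man who tests but only reports, or who returns the kit after 1 month. Control is scored on agreement, which can raise control uptake. Step 3 of the working shows that the net can go either way. This objection stands in full.
- **A reader might add invalid kits to the same error.** That does not hold. The outcome is taking a test, and a man whose own swab gave an invalid result took one. Control scoring does not ask for a valid result either.
- **The size is assumed.** This is true. At 5% of non-testers the false-positive rate barely moves, and 44% needs a rate of 20% that nothing in the article supports.
- **The article is condensed, and a return form may already ask who used the kit.** That is possible. But the outcome definition is printed with its numerator, denominator and window, and a kit used by someone else satisfies it. A question on a form changes nothing unless the scoring rule uses the answer.
- **Unobserved use is inherent in self-testing, and a returned kit is firmer evidence than a bare report.** This is fair, and it is a reason to keep the returned kit as a requirement. It does not show who used the kit.
- **A man who passed on his kit can say that he used it.** This is also true. Self-reported use reduces the error without removing it.

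**Conclusion.** The point holds for user identity only. As defined, HIVST uptake credits an enrolled man with a test that another person may have taken, and the control procedure has no equivalent error. Taken alone, the error raises HIVST uptake.

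The size cannot be stated from the document. The illustration of +2.3 to +9.0 points, with about a 7% to 44% chance of p<.05, rests on assumed misattribution by 5% to 20% of non-testers, no true effect, no other scoring error, and the plan's own sample size and design effect taken at face value. It shows that moderate misattribution would matter, not that it will occur. The direction of the endpoint's overall bias remains open.

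The definition should be amended because the weakness is differential by arm and cheap to reduce.

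**What to change.** 1. At kit return, or at the 1-month contact already planned, ask each man in the HIVST arm who used the kit: himself, another person, or not used.
2. In Primary Outcome Assessment, keep the returned kit as a requirement and add that a kit declared used by another person, or not used, is scored as not tested. State in advance how a returned kit with no answer is counted.
3. Report the any-returned-used-kit version as a sensitivity analysis.
4. Record invalid results, but do not score them as untested in the HIVST arm alone. That would create a new asymmetry with control.

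The cost is one question on the return form or 1-month questionnaire and one or two sentences in the outcome definition. The downside is that attribution is self-reported, so the error shrinks but does not vanish, and HIVST uptake may come out slightly lower. The change does not settle the separate mismatches noted in the working and objection: reports without a returned kit, and control scored on agreement.
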